### 2.4. Clusters Randomization

The clusters in this study are FM associations from the region of Extremadura (Cáceres, Almendralejo, Hervás, and Olivenza) in Spain. Each association will be randomly assigned to either the intervention group, which will participate in a structured physical activity program, or to the control group. The allocation sequence for the associations will be created using a computer-generated random number system (Random Number Generator tool; Google, LLC., Mountain View, CA, USA). Simple randomization will be applied, with no stratification, given the small number of clusters. The sequence will be recorded in a password-protected Excel file. Personnel responsible for enrolling associations and implementing the intervention will remain blinded to the allocation sequence until each cluster is assigned. The principal investigator (IP) will provide the group assignment immediately prior to the start of the intervention for each association, ensuring allocation concealment.

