#### 2.2.2. Recruitment

The sample size will be calculated based on one of the study’s primary outcomes, i.e., the impact of FM. Data from a previous study [22] that will be used as a reference evaluated the effects of a creative dance intervention on this outcome. In that study, the impact of FM was reduced by 1.16 points compared with the control group after six weeks of intervention.

According to the results obtained in the G*Power statistical power analysis software version 3.1.9.7 (Heinrich Heine University Düsseldorf, Düsseldorf, Germany), assuming an effect size of f(V) = 0.98, a power of 85%, and a significance level of 0.05, a sample size of 22 people per intervention group is estimated. However, considering an anticipated dropout rate of 10%, a total of 44 participants (22 per group) will be needed to observe a significant effect.

Therefore, the participants recruitment will take place between January and March 2026. Both groups will consist of women with FM (exercise group: *n* = 22; and control group: *n* = 22) recruited from different FM associations in the region of Extremadura.

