### 2.3. Randomization of Assessments

The assessments will follow a fixed sequence with alternating tests of the upper and lower limbs, thereby ensuring adequate rest periods to prevent cumulative fatigue and optimizing the overall time required for the evaluations. To reduce familiarization and learning effects, the sequence of specific conditions will be randomized. Randomization will apply to both the physical test conditions and the arithmetic cognitive task.

The physical tasks that each participant will complete at baseline (pre) and post-intervention will be scheduled across two assessment days:Day 1: Cognitive task (arithmetic-based counting test), handgrip strength, timed up and go test (TUG), arm curl test (ACT), and 30 s chair stand test (CST). Randomization: The random allocation sequence will be generated by an independent researcher using a computer-based random number generator (Random Number Generator tool; Google, LLC., Mountain View, CA, USA) and implemented via a password-protected Excel file. Simple randomization (0/1) will be used for Day 1 tasks. Personnel responsible for enrolling participants and conducting assessments will remain blinded to the random allocation sequence. Two aspects will be randomized for each participant: (1) whether the arithmetic subtraction task is performed at the beginning (coded as 1) or at the end (coded as 0) of the physical test sequence and (2) whether the motor task is performed as a single-task condition (coded as 0) or as a dual-task combined with the cognitive subtraction task (coded as 1). The handgrip test will be performed without dual-task condition due to its temporal execution characteristics;Day 2: Baseline resting Electroencephalography (EEG) and Heart Rate Variability (HRV), EEG and HRV combined with the Stimulus–Response (S-R) paradigm protocol, Short Physical Performance Battery (SPPB), and Agility Challenge for the Elderly (ACE). Randomization: Only the spatial orientation component of the ACE test will be randomized according to the recommendations of Lichtenstein et al. [23]. The random allocation sequence for this task will also be generated by the independent researcher, recorded in the same password-protected Excel file, and accessed by the researcher immediately prior to testing to ensure allocation concealment

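### Unrestricted randomisation of only four associations carries a 12.5% chance of an empty arm and a 50% chance of a 3:1 split; the allocation should be restricted to 2:2

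*Protocol article*

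**What the plan says.** Section 2.4 defines the randomised units: "The clusters in this study are FM associations from the region of Extremadura (Cáceres, Almendralejo, Hervás, and Olivenza) in Spain". It continues: "Each association will be randomly assigned to either the intervention group" or to control. The method is then fixed: "Simple randomization will be applied, with no stratification, given the small number of clusters". The principal investigator discloses each association's group just before that association starts. Section 2.1 repeats the association-level assignment.

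No section describes a block, matched pairs, a guaranteed 2:2 split, or what happens if all four associations fall in the same arm.

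Two other parts of the plan depend on the split. Section 2.2.2 sets the arm sizes: "a total of 44 participants (22 per group) will be needed to observe a significant effect". Section 2.13 plans a linear mixed model with group, time and their interaction as fixed effects and random intercepts for associations and participants. It also plans to report an intra-cluster correlation.

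**The concern.** With many units, simple randomisation gives arms of roughly equal size. With four it often does not, and it can put every association in the same arm. The group effect and the group × time interaction in Section 2.13 would then have nothing to compare. The practical response would be an unplanned redraw, which changes the allocation procedure after its result has been seen.

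A 3:1 result is less serious but much more likely. One arm is then a single association, so that arm says nothing about variation between associations.

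The stated reason does not support the choice. A small number of clusters is a fair reason not to stratify, since four units cannot usefully be divided into strata. It is also the situation in which the randomisation most needs to be restricted.

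**Working it through.** The plan gives no probability for the split, so there is no figure of its own to reproduce on this point.

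**Inputs**
- Four associations and two arms (Section 2.4).
- Independent allocation with probability p = 0.5. This is an assumption: the ratio is not written for clusters. It is the ordinary meaning of simple two-arm randomisation, and it fits the coding used elsewhere for the test conditions (Section 2.3: "Simple randomization (0/1) will be used for Day 1 tasks").
- For the power figures only: 44 women in total and a standardised effect of 0.98 (Section 2.2.2: "assuming an effect size of f(V) = 0.98, a power of 85%, and a significance level of 0.05"), read as Cohen's d with a two-sided test. Assumed ICC values are 0 and 0.05, because the document gives none.

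**Split probabilities.** There are 2⁴ = 16 equally likely allocations.

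| Associations in intervention arm | Count | Probability |
|---|---|---|
| 0 | 1 | 6.25% |
| 1 | 4 | 25% |
| 2 | 6 | 37.5% |
| 3 | 4 | 25% |
| 4 | 1 | 6.25% |

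- One arm empty: (1 + 1)/16 = 12.5%.
- 3:1 in either direction: (4 + 4)/16 = 50%.
- Not 2:2: 12.5% + 50% = 62.5%.

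**Sensitivity to p.** P(empty arm) = p⁴ + (1 − p)⁴ and P(not 2:2) = 1 − 6p²(1 − p)². Both are smallest at p = 0.5. At p = 0.4, for example, they are 0.0256 + 0.1296 = 15.5% and 1 − 6 × 0.16 × 0.36 = 65.4%. The 3:1 share alone then falls marginally, to 65.44% − 15.52% = 49.9%.

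**Reading 0.98 as d.** With two-sided alpha 0.05 and 85% power, a t test needs 20 per arm. Adding 10% gives 20 × 1.1 = 22, the stated size. Read literally as f with one numerator degree of freedom, about 12 in total would do. The d reading is therefore the one that fits the plan.

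**Power by split.** Cluster-level comparison with 4 − 2 = 2 df, two-sided critical t = 4.303, non-centrality = 0.98/SE.

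With 11 women per association (44/4), the variance of an association mean is v = ICC + (1 − ICC)/11, in units of the total variance.
- ICC 0: v = 0.0909. ICC 0.05: v = 0.05 + 0.95/11 = 0.1364.
- 2:2: SE = √[v(1/2 + 1/2)] = 0.302 and 0.369.
- 3:1: SE = √[v(1/3 + 1)] = 0.348 and 0.426. The variance rises by one third.

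If 22 per arm is kept under 3:1 (22 from one association, about 7 from each of the other three), the variance of the difference is ICC × (1 + 1/3) + (1 − ICC) × (1/22 + 1/22).
- ICC 0: 0.0909, SE 0.302. ICC 0.05: 0.0667 + 0.0864 = 0.1530, SE 0.391.

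| | ICC 0 | ICC 0.05 |
|---|---|---|
| 2:2, 11 per association | 43% | 33% |
| 3:1, 11 per association | 35% | 27% |
| 3:1, 22 per arm kept | 43% | 30% |

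**After restriction.** There are C(4,2) = 6 balanced allocations. Drawing one at random gives P(empty arm) = 0 and P(3:1) = 0. Each association is in the intervention arm in 3 of the 6, so its probability stays 1/2.

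**The case against.** *The authors may have meant an unstratified draw into two equal arms.* The equal arm sizes in Section 2.2.2 point that way, and the remark on few clusters can be read as explaining only the lack of stratification. This stands as doubt about intent, and on that reading the remark itself is sound. It does not rescue the text, which says simple randomisation and names no restriction. If a 2:2 draw was meant, the sentence still needs correcting.

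*Under 3:1 the arm sizes need not fail.* This stands. A reader might infer that a 3:1 split makes 22 per arm impossible. No section fixes a number per association, so 22 women from one association and about 7 from each of the others is arithmetically possible, if one association can supply 22. The document does not say whether it can. Because each assignment is disclosed only shortly before that association starts, recruitment could not readily be tailored to the split. The sizes are not guaranteed, and no more can be said.

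*Under 3:1 the group effect can still be separated from the association effect.* This also stands. It is tempting to say that the single-association arm makes the two inseparable. The model in Section 2.13 as described has one association variance common to both arms, and the three-association arm supplies 2 df for it. True inseparability would need one association per arm. What remains is reliance on a common variance that cannot be checked in the single-association arm.

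*The low power comes from having four clusters, not from the split.* Largely so: power is 43% or less in every cell of the table, including 2:2.

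**Conclusion.** The concern holds. As written, the allocation rule has a 12.5% chance of giving no comparison at all and a 50% chance of a 3:1 split. The only assumption behind these figures is independent allocation at probability 0.5, which is the most favourable value for both the empty-arm risk and the 62.5% chance of missing 2:2.

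The empty-arm risk alone makes correction before allocation necessary. A 3:1 split is a loss of precision and robustness, not a loss of validity. Its cost in power is 8 percentage points at ICC 0 and 6 at ICC 0.05 with 11 women per association, and none and about 3 points if 22 per arm is kept. These power figures also depend on the assumed ICC and on reading 0.98 as d; the split probabilities depend on neither.

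This is a flaw in a stated rule, not detail that an article leaves to a fuller document.

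**What to change.** In Section 2.4, replace the sentence on simple randomisation with:

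> One of the six possible 2:2 allocations of the four associations will be drawn at random in a single draw, without further stratification, and kept concealed until assignment.

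This costs one sentence and needs no extra participants or staff.

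Under a fixed 2:2 split, the last allocations become predictable once the earlier ones are known. Where scheduling allows, assignments should therefore be disclosed only after baseline assessment is complete in all four associations. This part is optional and has a price. Section 2.4 currently discloses each assignment just before that association starts, which permits staggered starts; waiting for all four could delay those that are ready early and lengthen the gap between their baseline and the intervention.

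The restriction removes the empty-arm and 3:1 risks. It does not cure the weakness of a comparison based on four clusters.

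### Fixed arm sizes of 22 and 22 do not fit concealed simple randomization of four whole associations: blind enrolment yields 22/22 in at most 37.5% of allocations

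*Protocol article*

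**What the plan says.** **Arm sizes.** Section 2.2.2 of the protocol article concludes that "a total of 44 participants (22 per group) will be needed to observe a significant effect", and then restates the arms as settled: "Both groups will consist of women with FM (exercise group: *n* = 22; and control group: *n* = 22". The abstract gives the same 22 and 22.

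**Unit and method of allocation.** Section 2.4: "The clusters in this study are FM associations from the region of Extremadura (Cáceres, Almendralejo, Hervás, and Olivenza) in Spain". Whole associations, not individual women, are allocated to exercise or control. The method is simple randomization without stratification, which the article justifies by the small number of clusters. It states no restriction to two associations per arm and no enrolment number per association.

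**Concealment.** Section 2.4: "Personnel responsible for enrolling associations and implementing the intervention will remain blinded to the allocation sequence until each cluster is assigned". And on timing, the same section adds this assurance: "The principal investigator (IP) will provide the group assignment immediately prior to the start of the intervention for each association, ensuring allocation concealment".

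**Related text.** Section 2.3 does mention staff who enrol participants, but the sequence hidden from them there is the order of test conditions, not the trial arm. Section 2.5 blinds evaluators and analysts to group. It does not mention those who screen and consent women.

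**The concern.** In a cluster trial the arm sizes follow from which clusters fall in which arm. A plan that names the arm sizes, but neither the cluster sizes nor the split of clusters, cannot deliver those arm sizes by design. If the split is unfavourable, staff must either accept different arm sizes or change how many women they take from an association once its arm is known.

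The second course would damage the comparison. Women who agree to join knowing that they will attend a dance class may differ from women who agree knowing that they will not. Several exclusions in section 2.2.1 call for judgement, such as a contraindication to exertion or any other condition affecting balance, and that judgement could be swayed by a known arm. Participants are not blinded (2.5), and the primary outcomes include the self-reported FIQR and EQ-5D-5L (2.12.1). Differences at entry that arise in this way are not repaired by having randomized the associations.

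**Working it through.** **1. The plan's own figure.** Inputs from section 2.2.2: "assuming an effect size of f(V) = 0.98, a power of 85%, and a significance level of 0.05", with 10% dropout. Sidedness is not stated, so two-sided is assumed.

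- Reading 0.98 as a standardized mean difference, the normal approximation gives n = 2 × (1.960 + 1.036)² / 0.98² = 18.7, so 19 per group. An exact t-test calculation gives 20.
- Dropout: 19 / 0.9 = 21.1, so 22. From 20, 20 × 1.1 = 22, or 20 / 0.9 = 22.2, so 23.

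Thus 22 per group is reproduced within rounding. Read literally as f(V), 0.98 would need only about 12 women in total. That is a separate matter and does not affect this point.

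**2. Splits of four associations.** Under simple 1:1 randomization there are 2⁴ = 16 equally likely outcomes.

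| Split | Outcomes | Probability | Arms with 11 per association |
|---|---|---|---|
| 2:2 | 6 | 37.5% | 22 / 22 |
| 3:1 | 4 + 4 = 8 | 50% | 33 / 11 |
| 4:0 | 1 + 1 = 2 | 12.5% | 44 / 0 |

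The figure of 11 is an assumption (44 / 4). The article gives no number per association.

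**3. Unequal associations.** For 22/22, the associations in the exercise arm must sum to 22.

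- Sizes 14/12/10/8 (assumed): only 14 + 8 and 12 + 10 work, so 2/16 = 12.5%.
- Sizes 16/12/9/7 (assumed): no combination works, so 0%.
- 44 women spread at random over four associations (simulated): exactly 22/22 in about 4.6%, and within 2 of 22 in about 21%.

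Equal enrolment is the best case. If every association enrols at least one woman, two sets of associations that both total 22 cannot contain one another. Four items allow at most six such sets, namely the six pairs, and all six pairs total 22 only when each size is 11. So 37.5% is a ceiling.

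**4. What 22 per arm would require of an association.** If two share the arm, 22 / 2 = 11 each. If one is alone, 22. If three share it, 22 / 3 = 7.3, so 7 or 8. The number depends on the allocation. Starting from 11 each in the 3:1 case, the lone association would need 22 − 11 = 11 further women and the other three would have 33 − 22 = 11 too many. Both adjustments would be made with the arm known. In the 4:0 case one arm has no association, so no adjustment can produce it.

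**The case against.** The best defence is the timing of disclosure. The arm is revealed immediately before the intervention starts. Baseline takes two assessment days and needs consent first, so the natural order is consent, baseline, disclosure, intervention, which is the usual protection against recruitment bias. Figure 1, not available here, may show that order, and a condensed article may leave such detail to the full protocol. The 22 per group may also be a planning number, with no rule to top up or cap an arm.

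Much of this stands, and it rules out two stronger readings. A reader might infer that 22/22 can be reached only by enrolling with the arm known. That is not so: 11 per association with a 2:2 split reaches it blind. A reader might also infer that women will be enrolled after disclosure, perhaps all 44. Nothing in the article says this.

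The defence does not remove the mismatch. The better the concealment works, the less the trial can steer towards 22 and 22. If the figure is only a planning target, the article should not present it as the composition of the arms while its allocation method misses it in most outcomes. Nor does the stated assurance depend on what an article may leave out: the sentence claiming concealment is printed, and the staff it names are those who enrol associations and deliver the intervention.

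**Conclusion.** The point holds as an inconsistency between stated rules, not as evidence that biased recruitment is planned. Under simple 1:1 randomization of the four named associations, blind enrolment delivers 22/22 in at most 37.5% of allocations, and that requires exactly 11 women in each. In the other 62.5% (10/16) the target is missed. In the 3:1 case (50%) it could be rescued only by adjusting enrolment with the arm known. In the 4:0 case (12.5%) there would be no between-group comparison.

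Whether recruitment bias would actually arise depends on an order of steps that the article does not state. If every woman is consented and baseline-tested before her association's arm is disclosed, and none is added later, the route is closed and what remains is unequal or empty arms. The figures rest on equal allocation probability for each association and on no unstated restriction to 2:2. The plan should be corrected; the flaw is not fatal to the design.

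**What to change.** 1. Replace the per-arm enrolment figure with a target per association set before allocation, for example 11 in each of the four.
2. Restrict the randomization to two associations per arm (six possible allocations). Otherwise drop the fixed 22/22 and state the unequal arms that may result. Step 1 alone is not enough: with 11 each and unrestricted randomization, half of the allocations still give 33/11.
3. Complete screening, consent and baseline in all four associations, lock the participant list, then disclose all four allocations together. Allow no later additions. Joint disclosure matters more once the split is restricted. With rolling disclosure the fourth arm always follows from the first three, and in 2 of the 6 allocations the first two share an arm and so give away the other two.
4. Extend the concealment sentence in section 2.4 to staff who screen and consent participants.

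The cost is rewording and a change in the order of steps. Early associations must wait until the last has finished baseline, and late volunteers are turned away.

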### 2.5. Blinding

Participants and personnel responsible for delivering the physical activity intervention will not be blinded due to the nature of the intervention, as they will become aware of their group allocation. However, the data analysts and evaluators will be blinded to group allocation to minimize bias in assessment and analysis bias. Group assignments will be coded as A or B in all data collection forms and databases, without revealing which code corresponds to the intervention or control group.

Unblinding will only be permissible in exceptional circumstances, such as a medical emergency requiring knowledge of the participant’s assigned group. In such cases, the IP for generating the allocation sequence will reveal the assignment following a documented procedure, and the reason for unblinding will be recorded.

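### The principal investigator gives out, and apparently generates, the allocation of associations with no stated separation from recruitment, so the claim that concealment is ensured is not supported

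*Protocol article*

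**What the plan says.** The unit of randomization is the fibromyalgia association. Section 2.4 names four of them and applies simple randomization without stratification.

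- **Generation (2.4).** "The allocation sequence for the associations will be created using a computer-generated random number system". The sentence is passive and names nobody.
- **Storage (2.4).** "The sequence will be recorded in a password-protected Excel file". It is not stated who has the file or the password.
- **Release (2.4).** "The principal investigator (IP) will provide the group assignment immediately prior to the start of the intervention for each association, ensuring allocation concealment".
- **Staff safeguard (2.4).** "Personnel responsible for enrolling associations and implementing the intervention will remain blinded to the allocation sequence until each cluster is assigned".
- **Emergency unblinding (2.5).** "the IP for generating the allocation sequence will reveal the assignment following a documented procedure".
- **Blinding after allocation (2.5).** "Participants and personnel responsible for delivering the physical activity intervention will not be blinded due to the nature of the intervention", whereas "the data analysts and evaluators will be blinded to group allocation to minimize bias in assessment and analysis bias".
- **Order of test conditions (2.3).** "The random allocation sequence will be generated by an independent researcher using a computer-based random number generator". This sentence concerns the Day 1 tasks. The same researcher also generates the sequence for the agility test on Day 2. Neither sentence concerns the allocation of associations to arms.

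**The concern.** Concealment means that whoever can influence which clusters or participants enter, and when, does not know the coming assignments. Section 2.4 claims concealment on the ground that the principal investigator releases each assignment late. Late release keeps the assignment from the staff who receive it. It does nothing about what the person releasing it already knows, and section 2.5 suggests that this person also produced the sequence.

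The protocol uses an independent person for the smaller matter, the order of tests, and states no such independence for the allocation on which the treatment comparison rests.

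If the principal investigator also has a say in approaching associations, scheduling their start or recruiting women, knowledge of the arm could affect who enters it. With four clusters, one association is a large share of the trial, and selective entry would be hard to detect or correct afterwards.

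**Working it through.** The protocol gives no figure on this point, so the check is mainly of the text.

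**Step 1: who distributes?** Section 2.4 is explicit that it is the principal investigator.

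**Step 2: who generates?** Section 2.4 does not say. Section 2.4 introduces IP as the abbreviation for the principal investigator, and section 2.5 uses it in the phrase on generating the allocation sequence. A word such as *responsible* appears to be missing. With it restored, the principal investigator is the generator. This is the only text that links anyone to generating the association sequence, but it is one damaged clause in a sentence about emergencies.

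**Step 3: which safeguards apply to that person?**

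| Safeguard | Section | Covers the principal investigator? |
|---|---|---|
| Enrolling and delivery staff do not know the sequence before assignment | 2.4 | Not stated; the same section has this person releasing the assignments |
| Release just before the intervention begins | 2.4 | No; it delays what others know |
| Evaluators and analysts blinded, groups coded A or B | 2.5 | No; it protects measurement and analysis, not entry |
| Independent researcher generates the sequence | 2.3 | Not applied to the associations |

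**Step 4: is the principal investigator separated from recruitment?** No section says so, and no section says the opposite.

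**Step 5: could the next assignment be guessed without the list?** Taking simple randomization as equal probability, each association has a 0.50 chance of either arm, and earlier assignments give no information about later ones. The splits of four associations are:

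- 2:2: 6/16 = 0.375
- 3:1 in either direction: 8/16 = 0.50
- 4:0 in either direction: 2/16 = 0.125

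There is no block structure to exploit. Concealment can be lost only through access to the list, which moves the probability of knowing an arm from 0.50 to 1. So the question of who generates and releases the list decides the matter.

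**Step 6: how much rests on one association?** Assuming that the 44 women of section 2.2.2 are spread evenly, 44/4 = 11 women per association, and 11/44 = 25% of the sample.

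**The case against.** The strongest reply is that the article already keeps those who enrol associations and those who deliver the program unaware of the sequence, and that concealment fails only if someone who knows the list also influences entry. No section gives the principal investigator that role. Release just before the intervention, read with pre-intervention assessments in sections 2.3 and 2.7, suggests that women would usually be enrolled and tested before the arm is disclosed. This has weight: it limits the likely harm. It does not rescue the claim, because the article does not state that enrolment and baseline are complete before release, and late release does not affect what the principal investigator knows.

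A second reply is that the planned mixed model tests group by time with random intercepts for associations and participants, so a stable baseline difference between associations is not itself the tested effect. That is right. A difference in how associations respond, for instance because one is more motivated, would remain.

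Three stronger readings are tempting, and the documents do not support them:

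- **That the principal investigator holds the list.** The article mentions a password-protected file but no custodian.
- **That the trial is open throughout.** Participants and trainers know the arm, but evaluators and analysts are stated to be blinded.
- **That the principal investigator can pick among several possible allocations by choosing the order in which associations are entered.** The four associations are named in advance, and the wording fits a single draw with staggered disclosure. Nothing says that associations wait for the next slot.

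**Conclusion.** The point stands as a gap between a claim and the procedure offered for it. Distribution by the principal investigator is explicit. Generation by the same person is the natural reading of section 2.5, but rests on that clause alone. Since no separation from recruitment is stated and no listed safeguard is said to cover this person, the statement that concealment is ensured is not supported.

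A reader might infer that the allocation will be manipulated or that the result will be biased. The documents do not show that. They show an unprotected route to selection bias, which becomes a breach only if the principal investigator influences the entry of associations or women. The size of any bias cannot be estimated from the article. The 11 women per association only indicates how much rests on each assignment, and it depends on the equal-size assumption. The change is worth making because it is cheap and replaces the stated procedure with a clearly better one.

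**What to change.** **Section 2.4.** State that the independent researcher of section 2.3 generates and keeps the allocation of associations. Write down the order of the four associations first, then make one draw against that list. Have this researcher release each assignment only after that association's participants are enrolled and have completed the baseline assessments.

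**Section 2.5.** Repair the damaged sentence and name the independent researcher, not the principal investigator, as generator of the sequence.

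**Cost.** A few sentences in two sections and a few minutes from someone already working on the trial. The downside is that the principal investigator learns the arms slightly later, which leaves less time for scheduling.
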